### Safety reviews

The trial will be conducted in two phases, with a dose escalation if no safety concerns arise during the low dose stage. Metformin dosing will begin at 500mg (children) and 850mg (adults) once daily for 5 days in cohort 1. Daily patient safety reviews will be performed by study doctors using clinical and laboratory data to decide whether patients are safe to continue taking the study drug.

The study drug will be stopped if participants: (1) request withdrawal from the study; (2) develop any AEs, including severe renal impairment (GFR below 30mL/min/1.73m
^2^), elevated lactate to ≥ 3 mmol/L, severe liver involvement (AST/ALT > 400U/L), severe diarrhoea (≥ 5 episodes of loose stool/day), persistent vomiting (≥ 3 episodes/hour or ≥ 4 / 6hours) and hypoglycaemia (blood glucose < 3.9 mmol/l or < 70 mg/dL); (3) develop severe dengue (defined as admission to intensive care unit); or (4) are intolerant of metformin.

All AEs occurring during the trial/or until the FU visit at around day 28 of illness, will be recorded in the CRF, and whether or not attributed to trial medication. Specific AEs are shown in
Table 1. Laboratory events will be graded according to Common Terminology Criteria for Adverse Events (CTCAE) definitions. Clinical events will be assessed as mild, moderate, or severe. If the event is serious and not only related to the progression to severe dengue, or is fatal, then a serious AE form must be completed and the OUCRU CTU notified within 24 hours.

In cases of discontinuation due to AEs, participants will be followed up until the events have resolved or stabilised. A Data Monitoring Committee (DMC) review will take place after day 5 data is fully available for the first ten patients enrolled in cohort 1. Following satisfactory safety review of the tenth patient, metformin doses for all remaining patients (cohort 2) will be weight-based; 5 days of 1000mg (500mg twice daily) for those weighing <60kg and 5 days of 1500mg (1000mg mane, 500mg nocte) for those weighing ≥60kg. All AEs and serious adverse events (SAEs) will be recorded and reported to the Ethics Committees (ECs) for review. Further DMC meetings will take place 6 monthly to review enrolment, AEs, treatment received and FU information, and any other requested data.

### Treatment and drug dispensation

Metformin will be kept in a dry location below 30°C, in a secure area. A study pharmacist will make up and label individual-participant treatment packs with a trial number. Each pack contains sufficient study drug for 5 days of treatment and will be distributed to study wards as required. All medication storage and administration will be regulated through the central pharmacy to ensure good quality and control of medication handling.

Patients will be recruited into either cohort 1 (low dose) or cohort 2 (high dose). Study drugs will be administered as directly-observed-therapy. Patients will take the first dose of study drug with a light snack as soon as possible after enrolment. The remaining doses will be taken after meals. In case of vomiting within 30 minutes of taking the treatment, one replacement dose will be given. However, if patients continue vomiting after taking the replacement dose, no extra drug will be given thereafter.

### Data collection

***Clinical evaluation.*** Patients will be reviewed daily until discharge. All clinical symptoms and signs will be recorded in the CRF. An ultrasound scan will be performed on day 5–6 of illness to detect evidence of fluid accumulation. General management decisions will be at the discretion of the attending ward doctors. Details of all AEs and SAEs will be recorded on specific forms, together with an assessment as to whether the events are likely to have been related to any treatment received. All SAEs will be reported promptly to the DMC and ECs according to policy.

***Laboratory evaluation.*** Full blood count (FBC) and POC glucose and lactate tests will be undertaken daily until discharge. An additional POC glucose test will be performed before their evening meal.

In addition, levels of serum albumin, transaminases (ALT/AST), creatinine, total cholesterol, HDL-cholesterol, LDL-cholesterol, triglycerides, and C-reactive protein (CRP) will be measured on alternate days. All tests will be done more frequently when clinically indicated.

Research samples collected daily until discharge will be used for dengue diagnostics (NS1 antigen detection and PCR assays). Residual blood from FBC samples will be collected for daily plasma viraemia levels. Serology tests (Capture IgM/IgG ELISAs) will be performed on enrolment (acute) and discharge/FU (convalescent) samples. Other laboratory investigations will include endothelial, inflammatory and lipid biomarkers (VCAM1, syndecan-1, leptin, adiponectin), using commercially available ELISAs and Luminex kits, immunological tests (T cell phenotype and functional analysis), and immunometabolism (AMPK phosphorylation). RNA will be extracted from a blood sample collected on study day 2, and will be sequenced to investigate gene expression in the metformin treatment group in comparison to the non-treatment group.

At day 28 of illness, final routine (FBC, biochemistry) and research blood samples will be taken to check whether patients have fully recovered from the acute dengue episode.

### Statistical considerations

***Sample size.*** This is an exploratory study focusing primarily on safety, and there are no preliminary data regarding the effects of metformin in dengue on which to base a sample size calculation. A target sample size of 60 patients was chosen based on clinical judgement and feasibility considerations. Using the trend in VCAM over time, which is one of the secondary endpoints, by assuming a slope of change in concentration over time at 0.34 (log
_2_VCAM concentration per day, data based on biomarkers of endothelial function in dengue), we conducted a power calculation using a t-test to compare effects on endothelial function between two groups. It is suggested this study will have a power of 80% to detect a difference of at least 0.023 (log
_2_VCAM concentration per day) in the slope of change.

***Statistical analysis.*** The primary analysis population will include all patients from cohort 1 and cohort 2, plus 60 controls as mentioned previously. Baseline characteristics and outcomes will be summarised for each treatment group. The cohort of patients enrolled in this study will form the active treatment group, while the control group will consist of overweight and obese dengue patients that participated in a matched cohort observational study, none of whom received metformin therapy. Continuous variables will be described using medians and quartiles, while categorical variables will be described in terms of frequencies and percentages.

The primary endpoint (number of AEs), will be compared between the treatment groups using negative binomial regression model. The clinical, biomarker, immunological will be compared between the treatment arms using linear regression or random effects model for continuous endpoints, and Cox regression for time-to-event endpoints (fever clearance time, time to first undetectable viremia measurement, time to first negative NS1 measurement). All comparisons will be adjusted for age, sex, and day of illness, as patients will not be randomized. For percentage increase in HCT and area under the curve of viraemia, comparisons will be also adjusted for the pre-dose value of the respective marker.

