### Metformin and dengue

Several of the aforementioned effects of metformin treatment have prompted consideration of its use as a potential dengue therapeutic. Firstly, the replication of dengue virus has been shown to be restricted by inhibition of lipid synthesis through AMPK activation
^24,
41^. Furthermore, metformin’s immunomodulatory effect, which facilitates NK cell activation, reduces T cell exhaustion profiles and enhances CD8
^+^ T cell memory, could help reduce levels of peak dengue viremia and shorten viral clearance times
^39,
41,
42^.

Metformin is rapidly absorbed and eliminated as an oral formulation and steady state is usually achieved within 24 hours. Metformin has been shown to decrease dengue viral genome copies in a dose-dependent manner
*in vitro* via activation of AMPK, with 90% reduction in NS1 secretion in infected cells after 24 hours of treatment
^41^. In obese/overweight adolescents, time to peak concentration and absorption, appears to be faster than non-obese children
^43^. In addition, anti-viral effects using a 5 day course of metformin has also been demonstrated in a mouse model of coxsackievirus B3 (CVB3) infection, through rapid action on AMPK activation
^44^.

Prevention of progression to severe dengue by attenuating the inflammatory mediators leptin and resistin is also plausible
^45^. Additionally, metformin could help reverse endothelial dysfunction, a hallmark feature of dengue pathogenesis, by improving endothelial-dependent vasodilation and reducing expression of endothelial vascular cell adhesion molecule (VCAM) and intercellular adhesion molecule 1 (ICAM1)
^24^. Recent observational evidence suggests metformin use in adult dengue patients with T2DM is associated with reduced risk of developing severe dengue (adjusted RR = 0.60, 95%CI 0.37-0.98)
^37^. However, the mechanisms underlying this association, and any relationship they have to obesity, require further investigation.

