### Design

This is an open-label study investigating metformin therapy in 60 overweight and obese Vietnamese adults (30 patients) and children (30 patients). Age range of 10 to 30 years, who are admitted to the Hospital for Tropical Diseases (HTD) in Ho Chi Minh City (HCMC), Vietnam, with positive non-structural protein 1 (NS1) rapid test and onset of fever <72 hours prior to admission.

We will investigate the effects of five days of metformin treatment on the grounds that the critical phase of disease usually occurs around the fifth day of illness.

The trial will be conducted in two phases, with a dose escalation between phases (
Figure 1). In the initial phase (cohort 1), five young adults (age ≥16) and five children (age <16) with body mass index (BMI) >25 kg/m
^2^ (BMI-for-age >1 standard deviation – SD) will be provided with a low dose of metformin once daily at 850mg and 500mg, respectively. If the five-day safety and clinical data of cohort 1 show no safety concerns, the study will progress to the second phase (cohort 2). This will include 25 adults and 25 children, who will be given a weight-based dose of metformin; 1000mg (500mg twice daily) for participants with weight <60kg, and 1500mg (1000mg mane, 500mg nocte) for those ≥ 60kg. Of note, the actual number of patients in each cohort will depend on the results of safety reviews. Recruitment is expected to happen over two dengue seasons, and discharged patients will be asked to return for a single outpatient follow-up (FU) visit around day 28 of illness.

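### The primary adverse event comparison pools the low-dose and higher-dose cohorts with no cohort term and with a split that is not fixed, so the escalated dose gets no estimate of its own

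*Protocol article*

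**What the plan says.** Under Statistical considerations, the article fixes the primary population: "The primary analysis population will include all patients from cohort 1 and cohort 2, plus 60 controls". It adds: "The cohort of patients enrolled in this study will form the active treatment group". The model is also named: "The primary endpoint (number of AEs), will be compared between the treatment groups using negative binomial regression model". On covariates it says: "All comparisons will be adjusted for age, sex, and day of illness, as patients will not be randomized". No term for dose or cohort appears, and no dose-specific comparison of the primary endpoint is described.

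The doses are in the Design section. Cohort 1 is planned as ten patients, half adults and half children, who "will be provided with a low dose of metformin once daily at 850mg and 500mg, respectively". Cohort 2 is planned as 25 adults and 25 children on 1000 mg a day (under 60 kg) or 1500 mg a day (60 kg or more). The section on treatment and drug dispensation itself labels the cohorts low dose and high dose.

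On cohort sizes, the Design section says that "the actual number of patients in each cohort will depend on the results of safety reviews". The Safety reviews section describes one step only: after a satisfactory review of the tenth patient, every remaining patient goes into cohort 2.

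**The concern.** The primary question is safety and tolerability, and the Discussion makes a larger randomised trial conditional on safety being established. The design escalates the dose only after a safety check, which presupposes that risk could depend on dose. The primary analysis then ignores dose.

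Two features make this more than a matter of presentation. First, the weights of the mixture are open, and the safety reviews that can change them use the trial's own AE data. Second, escalation requires that cohort 1 show no safety concern. In a trial that does escalate, the low-dose patients are therefore selected towards few AEs. If risk rises with dose, both features pull the pooled ratio towards no effect, which is the unsafe direction for a safety endpoint. The dose that most treated patients would receive has no estimate of its own.

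**Working it through.** **The plan's own figures.** The article gives no AE rate and no power or precision for the AE comparison, so there is no stated figure to reproduce. Its only power statement (80% for a VCAM slope difference of 0.023) comes without a standard deviation and does not bear on this point. All rate ratios (RR) below are assumptions.

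**Inputs from the Design section.** Treated 60, planned 10 in cohort 1 and 50 in cohort 2; controls 60.

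**1. Dilution.** With equal follow-up and balanced covariates, the expected count in the pooled group is the weighted mean of the two cohorts. With w = n1/60:

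RR_pooled = w × RR_low + (1 − w) × RR_high

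The excess lost is RR_high − RR_pooled = w × (RR_high − RR_low). If the low dose is not protective (RR_low ≥ 1), this is at most w × (RR_high − 1). At 10:50, w = 10/60, or one sixth of the excess.

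For RR_high = 2.0:

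| Split (cohort 1 : cohort 2) | RR_low = 1.0 | RR_low = √2 = 1.41 | RR_low = 2.0 |
|---|---|---|---|
| 10:50 (planned) | 1.83 | 1.90 | 2.00 |
| 20:40 (hypothetical) | 1.67 | 1.80 | 2.00 |
| 30:30 (hypothetical) | 1.50 | 1.71 | 2.00 |

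First cell: (10 × 1 + 50 × 2)/60 = 110/60 = 1.83. At 10:50 with no low-dose effect, high-dose ratios of 1.25, 1.5 and 3.0 pool to 1.21, 1.42 and 2.67.

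The sign can reverse. With RR_low = 2.0 and RR_high = 1.5, the pooled value is (10 × 2.0 + 50 × 1.5)/60 = 1.58, an overstatement.

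**2. Precision of a cohort 2 contrast.** If mean and dispersion are equal, the standard error (SE) of the log rate ratio is proportional to √(1/n_treated + 1/n_control). Relative to 60 v 60:

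- 50 v 60: √((1/50 + 1/60)/(2/60)) = √1.10 = 1.049
- 50 v 50: √((1/50 + 1/50)/(2/60)) = √1.20 = 1.095
- 40 v 60: √((1/40 + 1/60)/(2/60)) = √1.25 = 1.118
- 30 v 60: √((1/30 + 1/60)/(2/60)) = √1.50 = 1.225

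**3. Power, as an illustration only.** Assume a noncentrality of 2.80, which gives 80% power at two-sided 5% for 60 v 60 with the full effect. Cohort 2 v 60 controls has 2.80/1.049 = 2.67, so power Φ(2.67 − 1.96) = 76%. The model works on the log scale, so the pooled contrast with RR 2.0 v 1.0 keeps ln(1.83)/ln(2) = 0.874 of the effect: 2.80 × 0.874 = 2.45, power Φ(2.45 − 1.96) = 69%. If both doses act alike, pooling has 80% against 76%.

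**4. Cohort 1 alone.** SE = √((1/m + k)(1/10 + 1/60)), with assumed mean count m of 0.5 to 2 and dispersion k of 0.5 to 1. The 95% interval then spans a factor of about 2.0 to 3.2 each way, against 1.4 to 1.9 for the pooled 60. Ten patients support description, not a comparison.

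**The case against.** A reader might infer that pooling does understate harm at the escalated dose. The documents do not support that as a fact. The only dose-response statement, "Metformin has been shown to decrease dengue viral genome copies in a dose-dependent manner", is an in vitro antiviral finding and says nothing about AEs. Several events in Table 1 (low blood pressure, mucosal bleeding, raised transaminases, low platelets) are also features of dengue. If metformin works as hypothesised, a higher dose could reduce them. The sign of any bias is open.

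A reader might also infer that a large low-dose share is likely. The Safety reviews section gives no route to 20 or 30 low-dose patients followed by escalation, so those rows are conjecture. If escalation never happens, there is no mixing of the two cohorts.

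Further objections concern the remedy. Cohort 2 v control as the sole primary contrast could not be estimated if escalation were refused, whereas the pooled definition survives every outcome of the review. Cohort 2 itself mixes two weight-based doses. The design relies on contemporaneous controls, and comparing cohort 2 with all 60 would bring in controls recruited during the cohort 1 period. Finally, the study is exploratory, decisions during the trial rest on daily reviews and the Data Monitoring Committee, and an unseen analysis plan may hold by-cohort tables.

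Most of this stands, and it limits both the claim and the remedy. It does not remove the point. The article itself fixes the pooled primary population, so by-cohort tables elsewhere would leave the primary estimate a dose mixture.

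**Conclusion.** The point holds in limited form. The only stated primary estimate is a mixture over two dose levels with weights not fixed in advance, and the escalated dose gets no estimate.

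Whether this hides harm depends on an assumption that the documents do not settle, namely that AE risk rises with dose. If it does, and the low dose is not protective, the planned 10:50 split loses at most one sixth of the excess rate. That is modest: 1.83 for a true 2.0 in the worst case, and no loss if the doses act alike. The loss becomes serious only if the low-dose share grows well beyond ten patients, which the Design section permits but no section describes.

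The case for change is that a safety trial with a dose step should give a dose-specific answer, and that doing so costs little. It does not rest on a demonstrated bias.

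**What to change.** - Keep all patients in one negative binomial model, with the same covariates, and enter treatment as three levels: control, cohort 1, cohort 2.
- Pre-specify cohort 2 v control as a key contrast, reported beside the pooled metformin v control estimate. Keep the pooled estimate as the fallback if escalation does not occur.
- Report cohort 1 descriptively.
- Add a sensitivity analysis restricted to controls recruited concurrently with cohort 2.
- Reconcile the Design and Safety reviews sections on what determines the cohort sizes.

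This needs analysis and wording changes only, with no added patients or procedures. The price is precision: the cohort 2 contrast has an SE about 5% wider than the pooled one with 50 patients and all 60 controls. It is about 10% wider with about 50 concurrent controls, assuming that controls accrue in step with treated patients. With all 60 controls it is 12% wider if cohort 2 has 40 patients and 22% wider if it has 30. The contrast would still average over the two weight-based doses within cohort 2.

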**Figure 1. f1:**
[figure not shown]
Trial flow chart.

The 60 patients receiving treatment will be compared to 60 overweight or obese patients with standard of care (without treatment) recruited contemporaneously from the same wards, with the same enrolment criteria, in an ongoing observational study as the control arm.

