### Primary endpoint

The primary endpoint of this study is an evaluation of the safety and tolerability of metformin therapy in overweight and obese young adults and children with dengue. The number of clinical and laboratory adverse events (AEs) occurring during the five study days (
Table 1), will be compared between the treatment population and the non-treated controls.

**Table 1. T1:** Adverse events.

1- Worsening level of consciousness (fall in GCS ≥ 2 points)
2- Change in blood pressure (PP < 20 mmHg, SBP < 90 mmHg or unmeasurable BP)
3- Vomiting (≥ 3 episodes separated by 15 minutes/ 24 hours)
4- Epigastric abdominal pain
5- Diarrhoea (≥ 5 episodes/24 hours)
6- Mucosal bleeding
7- Rash, urticaria
8- Increased lactate (≥ 3 mmol/L)
9- Episode of hypoglycaemia (glucose < 3.9 mmol/L or < 70 mg/dL)
10- Increased liver enzyme (AST or ALT > 400 U/L)
11- Acute kidney injury (eGFR reduction of >50% or < 30 ml/mn/1,73m ^2^ or plasma creatinine >2 fold increase from baseline)
12- Thrombocytopenia (Platelet < 20.000/uL)
13- Other event, specify: [________________________________________]

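### The primary AE comparison does not say that controls share the treated arm's lactate, glucose and creatinine schedule or AE form, so unequal detection could make metformin look harmful

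*Protocol article*

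**What the plan says.** The Primary endpoint section fixes one counting window for both groups: "The number of clinical and laboratory adverse events (AEs) occurring during the five study days" "will be compared between the treatment population and the non-treated controls". Statistical considerations gives the model: "The primary endpoint (number of AEs), will be compared between the treatment groups using negative binomial regression model". Adjustment is for age, sex and day of illness.

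The Design section (under Figure 1) gives the comparator: "The 60 patients receiving treatment will be compared to 60 overweight or obese patients with standard of care (without treatment) recruited contemporaneously", these controls being enrolled "in an ongoing observational study as the control arm". Screening, enrolment and retention lists what the two studies have in common: eligibility criteria, wards, standard of care and dengue season, with recruitment alternating in two-week blocks. It also plans a blinded outcome assessment for all patients.

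Surveillance is described for this trial. Safety reviews says "Daily patient safety reviews will be performed by study doctors using clinical and laboratory data", in order to decide whether the study drug can continue. Data collection sets blood count, glucose and lactate daily until discharge, transaminases and creatinine on alternate days, and all tests more often when clinically indicated. It adds: "An additional POC glucose test will be performed before their evening meal". None of these sections says whether the control study follows the same schedule or uses the same AE form.

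**The concern.** Table 1 names twelve AEs. Five exist only if a laboratory or point-of-care test is done: raised lactate, hypoglycaemia, raised liver enzymes, acute kidney injury and thrombocytopenia. A review that decides whether to continue metformin cannot apply to untreated controls. In an open-label study, knowing that a patient is on the drug may also prompt an extra lactate or glucose test.

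If controls are tested less often, the primary rate ratio mixes drug effect with search effort. Blinded assessors can judge only what was recorded, and the three covariates do not measure testing intensity. The Discussion makes a larger randomised trial depend on safety being established, so a false signal of harm would have consequences.

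**Working it through.** **1. Which AEs are exposed.** The plan gives no power or error figure for the AE count. Its only power statement concerns the VCAM slope and does not bear on this point, so the first step is to compare the sections.

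- *Platelets and transaminases:* Secondary endpoints include platelet nadir and highest AST/ALT on illness days 3 to 8, and Statistical considerations compares such endpoints between groups. Controls must therefore have serial values of these, although the frequency is not stated.
- *Lactate and glucose:* the shared exclusion criteria imply baseline tests in controls. A baseline test cannot yield an AE, because patients with lactate above 2.0 mmol/L or glucose below 3.9 mmol/L are excluded, while the AE thresholds are lactate of at least 3 mmol/L and glucose below 3.9 mmol/L. Only follow-up tests count, and for controls these are unstated.
- *Creatinine:* follow-up testing in controls is also unstated.

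**2. Effect on one item.** Suppose treated patients have two glucose tests a day and controls one, over five days. Let p be the chance per test of a low value, with tests independent (assumption). The ratio of patients with at least one detected episode is g = [1 − (1 − p)^10] / [1 − (1 − p)^5].

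- p = 1%: 0.096 / 0.049, g = 1.95
- p = 2%: 0.183 / 0.096, g = 1.90
- p = 5%: 0.401 / 0.226, g = 1.77

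**3. Dilution in the total count.** If unequally detected items make up a share s of control AEs, the overall detected ratio is r = 1 + s(g − 1). With g between 1.77 and 1.95, r = 1.25 needs s = 0.25/0.95 = 26% to 0.25/0.77 = 32%. For r = 1.5, s must be 0.50/0.95 = 53% to 0.50/0.77 = 65%. One item alone is unlikely to produce the larger ratios.

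**4. Chance of a false finding of harm.** With no true effect, 60 per group, control mean μ0, treated mean μ1 = rμ0 and dispersion k:

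SE = √[(1/μ0 + k)/60 + (1/μ1 + k)/60], and P(harm) = Φ(ln r / SE − 1.96).

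Example with μ0 = 1, k = 0.5, r = 1.25: SE = √(2.8/60) = 0.216, ln r = 0.223, P = Φ(1.033 − 1.960) = 17.7%.

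Over assumed μ0 of 0.5 to 2 and k of 0.3 to 1.0 (nominal 2.5%):

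| Detected ratio r | False harm |
|---|---|
| 1.1 | 5–9% |
| 1.25 | 11–29% |
| 1.5 | 27–75% |
| 2.0 | 67–99.6% |

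**5. Would an exposure offset solve it?** A simulation of 400 trials per setting (treated mean 1 AE, k = 0.5, no true effect, constant event rate) gave these false-harm rates:

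| Setting | No offset | log(days) offset |
|---|---|---|
| Equal days and detection | 2.8% | 2.8% |
| 5 v 4 days observed | 17.5% | 2.3% |
| Controls detect 67%, equal days | 40% | 40% |
| Both | 66% | 35% |

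The offset repairs unequal time only, and only if the event rate is unrelated to discharge. If patients go home because they have recovered and have almost no later events, the raw five-day count is already fair. With 5 v 4 days the offset would then turn a true ratio of 1 into 4/5 = 0.80, favouring metformin.

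**The case against.** The strongest reply is that unequal testing is not documented. The article condenses a fuller protocol, and the control study's protocol and forms are not shown. Same wards, season and standard of care, alternating recruitment blocks and blinded assessment are real safeguards. The secondary endpoints already require serial platelets and transaminases in controls, and offsets are ordinary SAP content. Most of this stands. The blocks and shared criteria, however, address selection rather than detection, and an SAP cannot supply lactate, glucose or creatinine results that were never taken.

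A reader might infer more than the documents support:

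- *That there is no common time at risk.* The Primary endpoint section sets the same five-study-day window for both groups, and Safety reviews records AEs in this trial to about day 28. What ends at discharge is the daily review and routine testing.
- *That directly observed dosing keeps treated patients in hospital longer.* The article says only "Study drugs will be administered as directly-observed-therapy". It gives no length of stay for either group, so 5 v 4 days is purely an assumption. Observed dosing does not in itself create unequal detection.
- *That the ratio is biased upward.* No section says controls are tested less. If the schedules match, this problem disappears. If the control study's form asks about symptoms more closely, the bias could run the other way.

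**Conclusion.** The point holds as a conditional risk. The primary result is an open-label comparison of AE counts across two studies, and the article does not tie the control study to the same lactate, glucose and creatinine schedule or AE form. Drug-safety reviews exist in one group only, so heavier surveillance on metformin is the likely direction, but it is not proven.

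The size cannot be derived from the document. At a modest detected ratio of 1.1, false harm would be about 5–9%; at 1.25, about 11–29%. These ranges rest on assumed event rates, dispersion and detection gaps, and they describe what could happen, not what will. Lactate and glucose are the most exposed items, followed by creatinine; platelets and transaminases are less so. The defect justifies a specific change in the definition of the count. It does not justify making an exposure-adjusted rate the primary analysis.

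**What to change.** In Primary endpoint and Statistical considerations, define the primary count as laboratory AEs from tests scheduled on the same study days 1 to 5 in both studies, plus clinical AEs from the same daily form in both. State the control study's schedule, and align it and its AE form with this trial where recruitment still allows. List events found only by extra or drug-monitoring tests separately, by group.

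Keep the five-day count as the primary analysis. Add a model with log(patient-days observed to day 5) as an offset as a sensitivity analysis only, with the reason given: discharge is related to recovery.

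The cost is some wording in the plan, matching of two case report forms, and an amendment with ethics approval if the control study's schedule changes. The downside is that a few events leave the primary count, but they remain in the safety listing. If the schedules already match, a sentence saying so settles most of the point.
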